#### Medicines

For ambulatory care, oral amoxicillin DT (250 mg) will be used as recommended by the World Health organization for low HIV prevalence areas [7], Lucknow District being one of them. Amoxicillin DT (250 mg) will be packaged as PDK. PDK will be in platic zip locked 3 by 6 cm bags with either a green sticker (indicating use in children less than 12 months of age) or yellow sticker (indicating use in children between 12 and 59 months of age). PDK will have amoxicillin for a 5 day course + 2 additional doses for wastage (10 + 2 tablets `Green Kit` and 20 + 4 in `Yellow Kit`) (Table 4). Each kit will also have tablet paracetemol, instructions for use of medicines in Hindi, danger signs of pneumonia in Hindi and a card to mark number of days/doses per day of amoxicillin DT given. Each month ANM will be given 2 green and 2 yellow PDK through the CHC. Each CHC will get 25 PDKs/month and PHC will get 10 PDK/month. We will telephonically monitor the use of PDK and replenish them as and when needed to ensure uninterrupted supply.

**Table 4 Tab4:** WHO’s New Pneumonia Treatment Guidelines for Community Case Management

Age	Pneumonia in low HIV Prevalence areas	Pneumonia in high HIV Prevalence areas	Severe Pneumonia	Severe Pneumonia Danger Signs
2–12 Months 4-10 kg	1 Amoxicillin 250 mg tablet/twice a day/3 days	1 Amoxicillin 250 mg tablet/twice a day/5 days	1 Amoxicillin 250 mg tablet/twice a day/5 days	1st dose antibiotic, referral to health facility for supportive therapy
12–59 Months 10-19 kg	2 Amoxicillin 250 mg tablets/twice a day/3 days	2 Amoxicillin 250 mg tablet/twice a day/5 days	2 Amoxicillin 250 mg tablets/twice a day/5 days	1st dose antibiotic, referral to health facility for supportive therapy

*Source:* UNICEF. Amoxicillin Dispersible Tablets (DT): Product Profile, Availability and Guidance (July2014).Assessed:http://www.unicef.org/supply/files/Amoxicillin_DT_Product_Profile_and_Supply_Update.pdf

In this project Amoxicillin tablets will be procured from Indian based company which has certificate of being compliant with manufacturing standards recommended by the World Health Organization [8]. For the treatment of severe pneumonia, as recommended by F-IMNCI [9], Injectable Ampicillin and gentamycin (or third generation cephalosporin as second line of treatment) will be used which is available at the APHC/CHC. If they need additional supplies, it will be procured and supplied through the project.

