#### Trainings

##### Orientation of doctors, ANMs and on ASHA workers on prevalent community pneumonia management practices

The participants will be given the innovative `community orientation` to CAP using vignettes of real life cases of CAP, informed about community barriers to case management and their perceptions of health facilities. Thereafter, they will be shown the messages developed and told about the rationale behind each. They will be told about infrastructural strengthening, namely, PDK, PMC, PMU (Table 3). Additional training will be given to the care providers separately as given below.

**Table 3 Tab3:** Framework for Infrastructural Strengthening

Site	Infrastructural strengthening and purpose
Subcentre/PHC/CHC	PDK containing dispersible pediatric amoxicillin tablets (250 mg) PLUS instruction card will be provided by the project. Ten doses of amoxicillin (for a maximum of 5 days) will be kept in transparent envelop with *green sticker* for children below between 1 and 12 months and * yellow sticker* for children between 12 and 59 months. Each envelope will also have 4 tablets of paracetemol (500 mg). Within each envelope will have a small card with instructions for use of medicines on one side, and how to monitor a child with clinical pneumonia for improvement and deterioration on the other side will be kept. Instructions will be in Hindi.
APHC	PMC to treat pneumonia with fast breathing and stabilize &refer pneumonia with lower chest in-drawing with hypoxia (pulse-oximetry< 92%) and severe pneumonia. Project to provide: PDK, Pulse oximeter, spacer with baby mask, salbutamol inhaler. State Government Supply: Earmark ONE existing bed as *pediatric pneumonia bed,* storage facility for drugs, equipment and patient records and common facilities like 24X7 doctor-nurse; Injectibles: ampicillin, gentamycin, ceftrioxone, corticosteroid; Oral: antipyretics, co-trimoxazole; oxygen, face mask, suction machine and mucus extractors, laryngoscope, endotracheal-tube, ambu-bag, thermometer, pediatric blood pressure instrument.

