CHC	PMU to treat pneumonia with fast breathing and lower chest in-drawing and admit pneumonia with hypoxia (pulse-oximetry< 92%) and severe pneumonia. Project to provide: PDK, Pulse oximeter, spacer with baby mask, salbutamol inhaler. State Government Supply: Earmark TWO existing beds as *pediatric pneumonia beds,* storage facility for drugs, equipment and patient records and common facilities like 24X7 doctor-nurse; Injectibles: ampicillin, gentamycin, ceftrioxone, corticosteroid and vasopressors (dopamine), calcium, potassium, intravenous fluids like dextrose saline, Ringer Lactate; oral: antipyretics, co-trimoxazole; bronchodilators; oxygen, face mask,suction machine and mucus extractors, laryngoscope, endotracheal-tube, ambu-bag, thermometer, pediatric blood pressure instrument, nebulizer with nebulizer solutions of salbutamol, epinephrine and steroid, intravenous cannula, venous cut-open set, heater/warm air blowers for winter months.

*Abbreviations APHC* Additional Primary Health Centre, *PHC* Primary Health Centre, *CHC* Community Health Center, *PDK* Pneumonia Drug Kit, *PMC* Pneumonia Management Corner, *PMU* Pneumonia Management Unit

A brief refresher course on ARI module of F-IMNCI will be organized for doctors. Medical management of CAP in paediatric ward of a tertiary care teaching hospital will be demonstrated. Doctors will also be trained to record clinical data of CAP patients in simple to use case sheet prepared for the project. Training will be done in KGMU by F-IMNCI trained faculty.

A brief refresher course on ARI module will be also be organized for the ANMs in their respective CHCs. Investigators and faculty trained in F-IMNCI will impart training. ANMs will be trained to use drugs from PDK in the villages and SC and document it. They will also be trained to refer CAP with lower chest in-drawing or severe pneumonia by calling ambulance services by dialing 102/108. ANMs will be trained to conduct PAS using (a) case-stories (in video/text formats) (b) messages for early recognition of pneumonia, when and where to seek care, risk perception of delayed treatment or treatment from unqualified provider and also for recognition of the danger signs of pneumonia through the self-developed posters, audio and video messages as well as (c) inform the community about infrastructural strengthening, PDK, PMC, PMU and (d) respond to queries.

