### Adverse events monitoring

Approximately 5% of caregivers of cases of CAP who have received PKD will be contacted. They will be asked about their perceptions of the medicines and cards provided in the kit, whether the child required hospitalization or improved after taking medicines and if the child had diarrhea, rash, vomiting or any other complaints. This will be done by visiting their homes.

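### The green amoxicillin kit has no single lower age limit: the text gives none, Table 3 gives 1 month, and the cited dosing table starts at 2 months

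*Protocol article*

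**What the plan says.** The article describes who the green kit is for in two places and cites a dosing table for its contents:

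- **Medicines, text:** the green sticker is described as "indicating use in children less than 12 months of age". No lower age is given.
- **Table 3 (framework for infrastructural strengthening):** the green sticker is "for children below between 1 and 12 months". The wording is garbled, but the lower figure is 1 month.
- **Table 4, cited in the Medicines text right after the tablet counts:** the youngest row is "2–12 Months 4-10 kg".

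On who dispenses, the Trainings section says "ANMs will be trained to use drugs from PDK in the villages and SC and document it". On who is sent elsewhere, it says "They will also be trained to refer CAP with lower chest in-drawing or severe pneumonia by calling ambulance services". Study setting & participants covers caregivers of all children under 5 years and sets no lower age.

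On duration, the Medicines text says that amoxicillin follows the WHO recommendation for low-HIV-prevalence areas, and that each kit holds a 5-day course plus two spare doses. Table 4's low-HIV column gives 3 days. Table 3 calls 5 days a maximum.

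**The concern.** The kit is a fixed pack handed out by age band, partly outside any facility. If its lower age differs between statements, the same young infant can be inside the rule by one and outside it by another. Where the infant is inside the age rule but below the first row of the dosing table, the pack has no documented dose behind it. The stated ANM referral rule does not catch such an infant unless the illness is already severe enough to be referred.

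What is at stake is safe and uniform dispensing to the youngest infants, not the inference. Kits are supplied in every arm, and nothing here bears on the randomisation, the sample or the tests.

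The duration mismatch is a smaller matter of the same kind: the text names one recommendation and packs for a longer course without saying when the longer course applies.

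**Working it through.** **1. Reproduce the kit contents.** Inputs are the Medicines text and Table 4. Tablets = tablets per dose × 2 doses a day × 5 days, plus 2 spare doses.

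- Green: 1 × 2 × 5 = 10, plus 2 × 1 = 2, giving 10 + 2.
- Yellow: 2 × 2 × 5 = 20, plus 2 × 2 = 4, giving 20 + 4.

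Both match the text, so the kit is built on Table 4's doses.

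**2. Set the lower limits side by side.**

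| Source | Green kit or dosing row | Span | Part with no Table 4 row |
|---|---|---|---|
| Medicines text | under 12 months, no floor | 12 months | 0 to under 2 months: 2 of 12 |
| Table 3 | 1 to 12 months | 11 months | 1 to under 2 months: 1 of 11 |
| Table 4 | 2 to 12 months, 4 to 10 kg | 10 months | none |

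These are spans of age, not shares of children, cases or kits.

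**3. Look for a rule elsewhere that closes the gap.** The target population has no lower age. The ANM referral rule goes by chest in-drawing and severity. An infant of 5 weeks with fast breathing alone is therefore inside both the Medicines and the Table 3 age rules, is not referred under the stated rule, and has no row in Table 4.

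**4. What the fixed pack delivers.** The green dose is 1 × 250 mg × 2 = 500 mg a day. At Table 4's weight limits this is 500/10 = 50 mg/kg/day and 500/4 = 125 mg/kg/day. For an infant below the table, with weights of 2.5 to 3.5 kg (an assumption; the article gives none), it is 500/2.5 = 200 down to 500/3.5 = 143 mg/kg/day. That lies above the range the table implies. It shows direction only and is not a toxicity claim.

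**5. Duration.** The low-HIV column gives 1 × 2 × 3 = 6 tablets (green) and 2 × 2 × 3 = 12 (yellow). The kit holds 10 and 20 before spares, which is 4 and 8 more. Table 4's severe-pneumonia column does give 5 days.

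**The case against.** The strongest reply is that this is a condensed article. ANMs receive a refresher on the ARI module from trained faculty, operating procedures and training modules are to be written, and each kit carries an instruction card. An age check at dispensing would normally sit there, and none of that material is shown. Table 4 is also a reproduced guideline table, not a statement of who may receive a kit. This stands as a limit: the article cannot show that staff would in fact treat a young infant differently. It does not remove the conflict, because the age rule is stated more than once in the article itself and the statements differ. Table 4 is also the only dosing basis shown.

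Several stronger readings are tempting, and the documents do not support them:

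- **That the conflicting age is printed on the sticker.** The text describes a coloured sticker that indicates an age group. It does not say that an age is printed on it.
- **That the exposure can be counted.** From "Each month ANM will be given 2 green and 2 yellow PDK through the CHC" and the 331 ANMs in Table 1, 331 × 2 = 662 green kits a month. That is the ANMs' whole initial green stock for all infants. It is neither use nor a count of infants under 2 months.
- **That 5 days is wrong for most kits because ANMs refer the severe cases.** With "Each CHC will get 25 PDKs/month and PHC will get 10 PDK/month", and reading PHC as the 28 additional PHCs, ANMs hold 1,324 of 1,829 kits (72%). This fails because one standard pack serves all levels, 5 days is called a maximum, the card records the days given, and CHCs treat chest in-drawing. Packing for the longest course is a plausible reading.
- **That a 4 kg cut-off must be enforced at dispensing.** The kit rules go by age, and no weighing scale is listed among the supplies in Table 3.
- **That follow-up makes up for the gap, or makes it worse.** "Approximately 5% of caregivers of cases of CAP who have received PKD will be contacted" describes a sample taken after dispensing. It is not offered as an age check and weighs on neither side.

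**Conclusion.** The point holds as a dispensing-safety and consistency correction. The current text gives the green kit no lower age in one place and 1 month in another, and it cites a dosing table that starts at 2 months. Infants under 2 months (from 1 month, under Table 3) are therefore inside the kit's age rule without a dose in that table, and the stated ANM referral rule does not screen by age.

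The size is 2 of 12 or 1 of 11 months of the age span. The number of infants is unknown. The conclusion rests on reading the age statements as they stand and on no lower limit being shown elsewhere; unseen training material may already contain one.

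The duration point is secondary: the article omits a reason for packing 5 days. It does not say that every child receives 5 days. A reader might infer that the kit counts in the primary outcome, or the comparison of arms, are compromised. Nothing in the article supports that.

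**What to change.** Before kits are packed:

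1. State one range for the green kit, 2 to under 12 months, in the Medicines text, Table 3, the kit instruction card and ANM training. This matches Table 4.
2. Add age to the ANM referral rule: infants under 2 months go by the existing 102/108 ambulance route, unless the clinical lead documents a dose for them. Use the 4 kg figure as guidance only where a scale is available.
3. If the operating procedures or training modules already hold a lower age, the clinical lead should reconcile it with Table 4, and the one agreed limit should appear in all these places.
4. Secondary: add a sentence to the Medicines text saying when 3 days and when 5 days applies, for example 5 days for chest in-drawing treated at a CHC, if that is the intention.

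The cost is wording in two places in the article plus the card and training text. The green kit stays at 10 + 2 tablets; counts change only if the clinical lead chooses to pack 3 days. Design, sample and analysis are untouched. The downside is a few more referrals of very young infants; how these would fall across the arms cannot be told from the article.

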#### Process

##### Pre-intervention phase (6 months)

Standard operating procedures, training modules and data collection tools will be developed. Supplies (including drugs) will be procured. Working closely with the government, PMC and PMU will be established in APHC and CHC, respectively. Health staff will be trained. Baseline line Survey will be conducted in intervention and control areas to assess the burden of Acute Respiratory Illness (ARI)/CAP in under-5 children, care seeking pattern and behavior, socio-demographic conditions of households, health infrastructure and skills of service providers (KAP) for management of ARI/CAP. Survey will be carried out using population proportion sampling using 30 cluster methodology [10]. In all 2400 households will be selected from 240 villages.

#### Intervention phase (12 months)

Interventions that will be administered with existing health system have been described above. Time schedule is given as Additional file 1.

Description of Interventions is as follows:

*Intervention 1:* Organizing PAS using self-developed and validated IEC materials in PHCs and CHC monthly, conducted by a trained ANM (not involved with immunization) and project facilitator during routine immunization day. On this day about 30–50 parents with children come voluntarily at the CHC and APHC. The doctors at the APHC/CHC are also present at that time and besides supervising immunization will also give information to build awareness about pneumonia, if approached by the parents. A second ANM, not involved with immunization, will conduct IEC sessions in a separate corner of the immunization room or waiting area when a group of 10–15 caregivers have assembled.

During the PAS session, the ANM will use (a) case-stories (in video/text formats), (b) messages for early recognition of pneumonia, when and where to seek care, risk perception of delayed treatment or treatment from unqualified provider and also recognition of danger signs of pneumonia through the self-developed posters, audio and video messages as well as (c) inform the community about infrastructural strengthening, PDK, PMC, PMU and (d) respond to queries.

Dates for the PAS during immunization days will be fixed in advance with the administrative authorities. ASHA workers and ANMs will disseminate the date in their respective areas by word of mouth, through Gram Pradhan and Anganwadi Worker and mobilize the community.

The project staff will document the PAS proceedings, noting the number of persons who attended a particular session. The queries asked by attendees will be noted and over time a question and answer book will be prepared. On-site visits and telephonic contact will be made to validate conduction of PAS sessions. The project staff will conduct exit interviews of about 10% of the attendees noting their understanding of the materials explained to them and their satisfaction, using a pre-developed open-ended questionnaire (qualitative research methodology).

*Intervention 2:* PAS will be conducted during V.H.N.D. monthly by the ASHA worker for caregivers who congregate there using (a) case-stories (text formats) (b) messages for early recognition of pneumonia, when and where to seek care, risk perception of delayed treatment or treatment from unqualified provider and also recognition of danger signs of pneumonia through the self-developed posters, as well as (c) inform the community about infrastructural strengthening, PDK, PMC, PMU and (d) respond to queries.

*Intervention 3:* Combination of Both Intervention 1 & 2:

*Intervention 4:* This will be the Usual Care arm. In this arm only PDK, PMC and PMU will be established. No IEC will be done in the villages or APHC/CHC. Children in in the usual arm group will receive the same standard care and services provided to all children and their families residing in the area.

##### Quarterly health facility audit

This will be done to collect data on process Indicators and will be used for the establishment of Management information-system. Process indicators will be (i) utilization of PDK, PMC and (ii) conduct of PAS sessions in APHC, CHC and during VHND as well as numbers attending it. This will be done by the project staff. Data will be abstracted from records of PHC/CHC and SC for number of clinical pneumonia treated either as outpatients or inpatients or referred (with reasons and place) in last 1 month, and utilization of PDK and availability of medicines and equipment for the treatment of CAP (both provided through the project and supplied from the government). This information will be collated and shared with the Medical officer-In Charge of the health facility, Chief Medical Officer of Lucknow and office of Mission Director, National Health Mission.

#### Post intervention phase (6 months)

Post-intervention, primary outcome measures, e.g. utilization of public facility for management of CAP will be assessed through health facility audit. End line survey, similar to baseline survey, will be conducted to measure the changes due to proposed intervention in community’s preference of health providers for treatment of ARI/CAP. Data management, analysis and report writing will be done. Results will be widely disseminated. For widespread dissemination, study protocol and findings will be published in indexed peer-reviewed journals. Technology transfer will be done to the state government to scale up establishment of PMC, PMU and provide PDK plus implementing the most effective behavior change communication strategy for the entire state. Data will be accessible to public researchers after the study findings have been published.

### Data management & analysis plan

Data will be collected in pre-designed questionnaires preferably using electronic data collection system. Data quality assurance techniques and data cleaning procedures will be deployed before final analysis. Data will be analyzed using SPSS version 18 (Chicago, IL). Since this is a behavioral trial and no pharmacological intervention is being given, we do not plan to perform interim analysis.

Univariate distribution of baseline and outcome variables would be assessed by frequency counts. Outliers will be identified, reported and excluded from analysis if required. They would be compared between interventions using chi square test for categorical and Student’s t test and ANOVA for continuous variables. A *p* value of < 0.05 will be taken as statistically significant, using a two tailed distribution. Adherence to the intervention across each arm will be calculated and compared across the three arms (as one was a control arm). Good intervention is defined as > 75% adherence to the sessions in the duration of the project. Primary outcomes will be number of PDK kits distributed to children plus the number of children treated by government functionaries for acute respiratory infection (ARI) or pneumonia without PDK, using medicines available at the health facility in interventions given by ANMs/ASHA workers. If we find that the diagnosis of children being treated is not mentioned, then we fill this missing information by extrapolation from data where diagnosis is given for the same month and within the intervention arm, assuming that there would be similar proportion of cases with this diagnosis. We will compute the difference in the proportion of ARI/pneumonia treated in each intervention arm when compared to control arm in the intention to treat analysis. For the secondary outcome, we will compare the proportion of cases with ARI/pneumonia treated by government providers as their first choice in interventions given by ANMs/ASHA workers, as an intention to treat analysis. In the per-protocol analysis we will compare the proportion of cases with ARI/pneumonia treated by government providers as their first choice in interventions given by ANMs/ASHAs from those households which have participated in the baseline as well end line survey using paired t-test. As a sub-analysis, we will compare the mean, median and interquartile range of out of pocket expenditure for ARI/pneumonia in the baseline and end line survey within each arm. As a comparator, we will do similar analysis for cases who have suffered from diarrhea to assess whether changes in spending were a function of time or because of care seeking from government providers, which is most inexpensive.

A qualitative narrative of the process of establishment of the project will be given. Key informant and semi-structured interviews will be used to assess the level of satisfaction of stakeholders with (a) the services provided by public health facility augmentations and (b) IEC campaign strategies. Qualitative analysis techniques will be used for this data analysis.

Primary outcomes will be (a) number of patients of CAP treated by ANMs/doctors with medicines from PDK OR treated PMC OR PMU and (b) health service providers’ preference for treatment of CAP/ARI. For health facility utilization, the data will be abstracted periodically from the records maintained there. Feedback will be given to each facility on the process indicators within a month. For health provider preference, data from base line and end-line multistage cluster surveys will be used. At the end of the project the primary outcome measures will be compared in interventions given by ANMs/ASHA workers, using tests of proportion.

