### Study setting & participants

This study will be conducted in rural areas of Lucknow district, which is the capital of state of Uttar Pradesh in North India. Lucknow district has a population of 4,589,838, of which 33.79% are rural [6]. Here, there are 8 rural administrative blocks. Public health system for each of these blocks comprises of at least one (and in one block two) community health center (CHC) with outpatient care by doctors including pediatricians and 30 inpatient beds. Under each CHC are additional primary health centers (PHCs) for approximately 100,000 population with outpatient facilities and 4 beds. The lowest level of care is through a sub-center with an ANM. There is one subcenter for about 5 villages. Existing health infrastructure in Lucknow block at the initiation of the project is given in Table 1.

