### Study design

A Community Based Open Labeled Behavioral Trial conducted in 2 by 2 factorial design (Table 2) and geographic distribution of these areas is given (Fig. 1). Two blocks, proportionately equal in terms of number of ASHA workers (roughly equal to be number of villages) have been purposively paired and then randomly assigned to an interventional arm. Health infrastructure in each intervention arm is given in Fig. 2.

**Table 2 Tab2:** Design of the project

		PAS at APHCs/CHCs	
		Yes	No
PAS on VHND PLUSVillage IEC	No	Gosaiganj Block and Mall Block (Intervention1)	Bakshi Ka Talaab Block and Chinhat Block (Intervention 4)
	Yes	Malihabad Block and Mohanlalganj Block (Intervention3)	Sarojininagar Block and Kakori Block (Intervention2)

*Abbreviations PAS* Pneumonia Awareness Session, *VHND* Village Health and Nutrition Day, *IEC* information education communication, *PHC* Primary Health Centre, *APHC* Additional Primary Health Centre, *CHC* Community Health Center

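### Four pairs of blocks were allocated, one pair per arm, but arms are compared with chi-square tests and tests of proportion that ignore clustering, so a between-arm p < 0.05 is not valid

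*Protocol article*

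**What the plan says.** On allocation, the section *Study setting & participants* states: "Here, there are 8 rural administrative blocks". Under *Study design*, two blocks with similar numbers of ASHA workers "have been purposively paired and then randomly assigned to an interventional arm". Table 2 then shows two blocks in each cell of the 2 by 2 layout; the control cell, for example, reads "Bakshi Ka Talaab Block and Chinhat Block (Intervention 4").

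On analysis, the section *Data management & analysis plan* says that baseline and outcome variables are to be "compared between interventions using chi square test for categorical and" t test or ANOVA for continuous ones, with two-tailed p < 0.05 as significant. The between-arm contrast is also fixed there: "We will compute the difference in the proportion of ARI/pneumonia treated in each intervention arm when compared to control arm". Later in the section, "the primary outcome measures will be compared in interventions given by ANMs/ASHA workers, using tests of proportion".

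Clustering appears only as a way of sampling the survey: "Survey will be carried out using population proportion sampling using 30 cluster methodology" (section *Pre-intervention phase (6 months)*), with 2400 households in 240 villages. The article names no ICC, design effect, cluster-level summary, mixed model, GEE or robust standard error.

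**The concern.** Chi-square tests and tests of proportion take the variance from the number of cases, as if each case were an independent observation of its arm. Here the intervention was given to whole blocks, and blocks were allocated in pairs. Children in one block share facilities, staff and local care-seeking habits. A difference between two arms therefore contains the ordinary difference between their blocks, which the stated tests leave out of the standard error. The survey adds a further level, the village.

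A decision hangs on the result. The sections *Post intervention phase (6 months)* and *Ethics and research governance* say that the communication strategy found most effective will be extended to the state and to the district. Block differences that have nothing to do with the awareness sessions could select that strategy and give it a small p-value.

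This is not a detail left to an unseen analysis plan: the article itself fixes the tests, the threshold and the contrast.

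**Working it through.** **The plan's own figure.** The article states no sample size, power or ICC, so no derived figure can be reproduced. Its only error rate is the nominal one: 2(1 − Φ(1.96)) = 0.05, which holds if all observations are independent (ICC = 0).

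**Inputs from the article.** 8 blocks, 4 pairs, 4 arms, 2 blocks per arm (*Study design*, Table 2). Survey of 2400 households in 240 villages (*Pre-intervention phase*): 2400/8 = 300 households and 240/8 = 30 villages per block, and 2400/240 = 10 households per village.

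**Assumed inputs.** ICC between blocks of 0.005, 0.01 and 0.02. Cases per block m of 30, 150 and 300; m = 300 would need one case in every surveyed household.

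**False-positive rate, one arm versus control.** Design effect DE = 1 + (m − 1) × ICC if the two blocks of an arm vary independently. If the pair acts as one unit, m is replaced by 2m. True rate = 2(1 − Φ(1.96/√DE)).

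| m per block | ICC | DE, blocks independent | Rate | DE, pair as unit | Rate |
|---|---|---|---|---|---|
| 30 | 0.005 | 1.15 | 6.7% | 1.29 | 8.5% |
| 30 | 0.01 | 1.29 | 8.4% | 1.59 | 12.0% |
| 30 | 0.02 | 1.58 | 11.9% | 2.18 | 18.4% |
| 150 | 0.005 | 1.75 | 14% | 2.50 | 22% |
| 150 | 0.01 | 2.49 | 21% | 3.99 | 33% |
| 150 | 0.02 | 3.98 | 33% | 6.98 | 46% |
| 300 | 0.005 | 2.50 | 21.5% | 4.00 | 32.7% |
| 300 | 0.01 | 3.99 | 32.6% | 6.99 | 45.8% |
| 300 | 0.02 | 6.98 | 45.8% | 12.98 | 58.6% |

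Worked line: m = 300, ICC = 0.01 gives DE = 1 + 299 × 0.01 = 3.99; 1.96/√3.99 = 0.98; rate = 32.6%. A beta-binomial simulation (20,000 runs, assumed proportion 0.20, independent blocks) gave 32.5% for this case. At the favourable end, m = 30 and ICC = 0.001 give only 5.3%.

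**Facility counts.** For counts, the relevant quantity is the between-block coefficient of variation (CV): DE = 1 + (mean count) × CV². With an assumed 300 cases per block, a CV of 0.05 gives DE = 1.75 and 14%; a CV of 0.10 gives DE = 4.0 and 33%.

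**What the allocation can support.**
- Pair as unit, arm versus control: 1 against 1, so 1 + 1 − 2 = 0 error df.
- Pair as unit, factorial main effect: 2 against 2, smallest two-sided permutation p = 2/C(4,2) = 2/6 = 0.33. Mean, two main effects and interaction use all four pairs, so 4 − 4 = 0 error df.
- Block as unit, arm versus control: 2 against 2, smallest permutation p again 0.33.
- Block as unit, main effect: 4 against 4, smallest permutation p = 2/C(8,4) = 2/70 = 0.029.

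**Precision at block level.** Error is pooled over all eight blocks, so 8 − 4 = 4 df and t = 2.776. The 95% half-width, in units of the between-block SD, is 2.776 × √(1/2 + 1/2) = 2.78 for arm versus control and 2.776 × √(1/4 + 1/4) = 1.96 for a main effect. One baseline covariate leaves 3 df (t = 3.182), and the main-effect multiplier becomes 3.182 × 0.707 = 2.25, applied to the SD that remains after adjustment.

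**The case against.** Four points on the other side deserve a fair hearing.

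**The size is not known.** A reader might infer that the planned tests are bound to give false positives far too often. The article supports only the direction. With few cases per block and a small ICC the excess is slight, and both quantities are assumptions. This stands: the rates above are a range, not an estimate.

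**A factorial block-level analysis might seem to restore valid inference.** It does not do so fully. The 4 df come from differences between the two blocks inside each pair, and those blocks were chosen to be similar in ASHA numbers. If pairing made them alike, within-pair variation understates variation between pairs and even these intervals are too narrow. They hold only if blocks are treated as independently allocated, which is not how the allocation is described. Nor should the gain be overstated: estimating error from the two compared arms alone (2 df) gives 4.30 SD for arm versus control, but the like-for-like comparison with pooled error is 2.78 against 1.96.

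**A reader might infer that the plan ignores its factorial structure.** That goes too far. The repeated phrase about interventions given by ANMs or ASHA workers can be read as the two factors. The section on behavior change communication and the ethics section also ask an arm-level question: the smallest effective package, and which of facility, village or combined sessions does best. Main effects alone do not answer it, so they should be added to the arm contrasts, not put in their place.

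**Baseline adjustment is not available throughout.** The survey has a baseline. Drug kits, management corners and management units do not exist before the project, so their use has none.

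None of this rescues the stated tests. The article does not use the words individual-level, but chi-square tests and tests of proportion on cases take their variance from case counts, and no analysis of block summaries is described.

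**Conclusion.** The concern holds and should be corrected before analysis. Four allocated units, one per arm, cannot support a between-arm p < 0.05 from tests that ignore clustering. The direction of the error is certain for any positive between-block variation. Its size rests on assumed ICCs and case numbers: roughly 7% to 46% in place of 5% over the range shown with independent blocks, and 8.5% to 59% with the pair as the unit. Independently of those assumptions, arm versus control has no error df at pair level and cannot reach p < 0.05 by permutation at block level. The documents do not support the stronger conclusion that a block-level factorial analysis gives fully valid tests; it gives more defensible intervals under a stated condition.

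**What to change.** In *Data management & analysis plan*:

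- Replace the unadjusted between-arm tests with an analysis of eight block-level summaries, and show all eight values. This also absorbs village clustering. Adjust for baseline in the survey outcome only. For facility counts, name the denominator used, since the article gives none by block.
- Report the two factorial main effects (facility sessions yes/no, village sessions yes/no) with t-based intervals on block-level df: 4 without a covariate, 3 with one.
- State that these intervals hold only if blocks are treated as independently allocated, because at pair level the factorial model is saturated and the main-effect permutation p cannot fall below 0.33.
- Present arm-versus-control differences and the choice of most effective strategy as descriptive, with no p < 0.05 claim.

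The cost is revised wording and simple code, with no new outcome data; the process indicators already follow kit use by block and quarter. The downside is wider intervals and fewer significant results.
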